#### Precision

We are testing the prevalence of cholinesterase concentrations likely to impact on health, estimated at 35% [59,60]. We are able to recruit 360 respondents in each country. We calculate that 360 respondents will allow us to verify this 35% prevalence, with 95% confidence intervals lying between 28% and 42%.

#### Reporting

The data for each country will be reported separately to inform national stakeholders and policy makers. If the data are sufficiently similar across countries, we shall consider a combined analysis in a multilevel model. Otherwise, we shall undertake a meta-analysis to accommodate high heterogeneity.

We believe that abnormal AChE levels anywhere within our estimated range (28%-42%) will suffice as triggers to modify behaviour. Our models will identify behaviours that might usefully be targeted.

### Operational considerations

Certain financial and logistical constraints mean that we cannot apply probability sampling to all levels of participant selection in a way that would have been desirable. The small project budget dictated the decision that each ASEAN country team would limit fieldwork to the province in which the university is located, rather than attempting a country-wide sample. It was further decided to opt for purposive rather than probability sampling of three districts in each province because of exceptional constraints applying at the time of fieldwork. Fieldwork must start in mid-2021 because of deadlines imposed by the funder. It must take place against the background of the COVID-19 pandemic. For these reasons it is necessary to select districts with a sufficient volume of vegetable production in which fieldwork is feasible when travel and safety are considered. We will use already published data to provide information on where the selected districts fit within the spectrum of districts in the study provinces. Because of serious civil disturbances and armed conflict in Shan State we have been forced to abandon the planned Myanmar arm of the study.

### Research ethics

It was a condition of GCRF funding that the project received a favourable ethical opinion from the Swansea University Research Ethics & Governance Committee (Chair [name]; Email [contact]; website: https://www.swansea.ac.uk/medicine/research/ethics/#bbq=on). The research protocol was approved on 6^th^ January 2021 by the College of Human & Health Sciences Research Ethics Sub-Committee (approval reference number 151220b). The Swansea REC approval allowed project preparatory work to continue, but required additional approval from ethics committees in each of the participating Asian countries before fieldwork in that country could begin. Favourable opinions have been obtained from Mahasarakham University Ethics Committee for Research Involving Human Subjects (Ref. number 127/2020; date 22/4/2020), the University of Health Sciences Research Ethics Committee, Vientiane (Ref. number 137; date 29/3/2021)., and the Institutional Ethics Committee of Hue University of Medicine and Pharmacy (Ref. number H2021/420; date 12/8/2021).

All participants in the study will be given an information sheet and sign a consent form or give a thumb print. The information sheet explains that participation is voluntary and that participants can withdraw at any time, up until a final confirmation of consent after interview and blood tests are completed. It explains the (low) risk of infection associated with finger prick blood tests, offers assurances that confidentiality and anonymity will be preserved, that data will be stored securely, that no blood samples will be retained by the researchers, and that names and addresses will be used only for the purpose of contacting participants to advise of blood test results and, if necessary, to refer them to a local health professional for advice and assistance.

Consent for this study involves consenting to receive blood test results, and agreeing that, if the results show high pesticides exposure, participants’ names can be passed to the local health service. The latter will be done by contacting local staff in the public healthcare systems of the three countries involved. Following the interviews, a health information sheet will be given to participants with advice for handling, using, storing and disposing of pesticides and containers, as above. This will be given to all who complete an interview, regardless of whether they also complete the blood test and are included in the study. As is common in field studies a small reward for respondents will only be payable on completion of the interview and blood test; this is made clear in the information sheet.

### Service user involvement

Health effects of pesticides exposure are a major concern in farming communities, and feedback from those involved in the Thai pilot study helped shape the final research design. The study will enlist the help of local health and social care staff and village guides to recruit and meet participants. There will be feedback and assistance for participants found to have high exposure.

## Fieldwork process

Sampling of cases is based on purposive sampling of three groups of villages/districts in each of the three countries and subsequent recruitment of agricultural workers. The three districts (or groups of villages) will be selected so that taken together they cover a range of small and large farms and spread of vegetable crop types.

Respondents will be sampled randomly from the population of farm workers in the village/district.

As a first step health or local government personnel familiar with the district will compile a list of workers involved in vegetable production in the village/district. The list will include all members of households aged 18 and above who work regularly as farmers. Candidates may be natives or migrant workers, but must be fluent in the main language of the study country. They will be encouraged to participate through the offer of a small reward, a cash payment of less than £1 GBP payable on completion of the study. The list will comprise information on name, large or small farm and gender. The number of households and people on the list will be noted.The research team will use a randomising procedure to select from the list 120 first choice workers’ households and 30 reserves (with the latter listed in order).The health or local government staff assisting with the project will be advised of the selection. They will approach the first 120 named candidate households selected by the research team as first choices for inclusion to ask whether a volunteer adult household member is willing to meet with the research team to discuss participation in a research project on pesticides use. Information sheets will be distributed.Those volunteering will be contacted by researchers. The content of the information sheet will be explained and opportunities to ask questions provided. Those indicating their consent to participate will be screened to determine whether they meet the study inclusion criteria (which include a check that only one member per household takes part). Those selected will sign or provide a thumb print on a consent form.The main interview will be conducted either immediately or within a few daysWhen interviews are completed, consent to take blood samples will be confirmed. Only participants who agree to both interview and blood sample will be included in the study. Capillary blood samples will be taken using finger-prick lancets. In Thailand local public health staff measure AChE levels of farm workers routinely as part of a government health promotion initiative, using test kits identical to those purchased from the Thai GPO for the study. If tests were completed within the past 4 weeks these results will be used for this study, as was the case in the pilot study. If no such data are available for consenting participants from the local health service, finger-prick blood tests will be undertaken after the interviews.In the event that candidates from the original 120 selections fail to meet the research team, are found to be ineligible or do not consent to participate in all stages of the study, additional candidates from the reserve list will be approached one by one to make up the numbers.Participants completing the interviews will be given a health protection information sheet detailing dos and don’ts of safe pesticides use.Participants completing the blood tests will be advised of where to seek help if any adverse effects (such as infection) arise. They will also be told how they will be notified of the blood test result and that local health staff will advise them on necessary treatment or behavioural change. They will be given the small study reward.

Agricultural workers eligible for inclusion in the study must:

be involved in cultivating vegetables as a main crop for commercial sale for at least 10 months a year (fruit may be included as a secondary crop);have applied pesticides to crops in the last 3 weeks.be aged 18 or above

Workers will be excluded if they:

work mainly with organic vegetables or fruits;cultivate hydroponics;cannot communicate in the primary native language of the study country;are from the same household as an already-recruited participant.

We have added the requirement that workers should have used pesticides in the last three weeks because it is known that, following exposure to organophosphates, AChE levels begin to rise to near-normal levels after that period [64].

A flow diagram illustrating the fieldwork process is shown in Fig 1.

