#### Clustering

We will interview only one person from any one household to avoid data replications on household-level behaviours, such as laundry; this also allows us to use a single intra-cluster correlation coefficient (ICC) for responses from the same district. With no ICC available from our single-district Thai pilot study, we have used the unadjusted median ICC observed in primary care studies across a range of variables: (interquartile range [IQR] 0 to 0.032) [61], and set the ICC here to 0.01. With m = 120 interviews per district, our design effect, calculated as 1+(m-1)*ICC [62] is 2.19; this compares with design effects values ~1.5, as reported in surveys of developing countries [63]. Our confidence intervals are thus inflated by a multiplicative factor of 1.48 over those based on the assumption of independent responses; this adjustment accounts only for clustering within districts (groups of villages).

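### Respondents are described as a random sample of farm workers, but the procedure draws households at random and interviews a volunteer from each

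*Protocol article*

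**What the plan says.** All of the following is from the protocol article.

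- **Summary statement (Fieldwork process):** "Respondents will be sampled randomly from the population of farm workers in the village/district".
- **Sampling list (Fieldwork process, recruitment steps):** "The list will include all members of households aged 18 and above who work regularly as farmers". It carries name, farm size and gender. Totals are kept: "The number of households and people on the list will be noted".
- **Random draw (same steps):** the team will "select from the list 120 first choice workers’ households and 30 reserves (with the latter listed in order".
- **Choice of person (same steps):** local staff ask each drawn household "whether a volunteer adult household member is willing to meet with the research team". The volunteer is then screened. Candidates who do not turn up, are ineligible or decline are replaced one by one from the reserve households.
- **One per household (Clustering):** "We will interview only one person from any one household to avoid data replications on household-level behaviours".
- **Eligibility (Fieldwork process):** among other criteria, respondents must "have applied pesticides to crops in the last 3 weeks".
- **Disclosure:** Operational considerations says that "we cannot apply probability sampling to all levels of participant selection". Limitations repeats this for both site and respondent selection.
- **Precision:** 360 respondents per country, expected prevalence 35%, 95% interval 28% to 42%.

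**The concern.** The summary sentence and the recruitment steps describe different designs. In the steps the randomised unit is the household, and the person interviewed is whoever comes forward. A worker's chance of inclusion then depends on who volunteers and, depending on how the draw is made, on how many workers share the household.

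This matters because the first three objectives are worker-level descriptions: the prevalence of high exposure, the proportion with suboptimal behaviours, and levels of knowledge, protective behaviour and self-reported illness. The article itself gives reasons why volunteering might relate to these outcomes:

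- Participation brings a blood result and, if exposure is high, referral (Research ethics; Service user involvement). A symptomatic or worried member has more reason to come forward.
- Background names sprayers and mixers as a high-risk group, and the fourth objective presumes that cholinesterase may vary with individual practice.
- In Thailand, routine test results from the past 4 weeks are reused. Such a result may already be known when the household decides who volunteers. This route is described for Thailand only, so any selection could differ between countries that the study sets out to compare.

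An analysis plan cannot restore a random step that the fieldwork omits.

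**Working it through.** **1. The procedure, step by step**

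| Step | Unit | How chosen |
|---|---|---|
| Districts, 3 per country | District | Purposive |
| 120 first choices and 30 reserves | Household | Random |
| Person within household | Worker | Volunteer, no random step stated |
| Replacement after ineligibility or refusal | Household | Next on the reserve list |

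The third row contradicts the summary sentence. By the fourth row, no step tries a second eligible worker in the same household.

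**2. The plan's own interval**

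Inputs: p = 0.35, n = 360 (Precision); m = 120, ICC = 0.01 (Clustering).

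- Design effect = 1 + (120 - 1) × 0.01 = 2.19; square root 1.48.
- Half-width under independence = 1.96 × √(0.35 × 0.65 / 360) = 4.93 points.
- Inflated half-width = 4.93 × 1.48 = 7.29 points, giving 27.7% to 42.3%.

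This reproduces the stated 28% to 42%. By the article's own account the inflation covers district clustering only. It has no term for selection within the household.

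**3. Possible size of volunteer bias (all inputs assumed)**

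Take two eligible workers per household with average prevalence 35%, differing by d points. The higher-risk worker volunteers in a share s of households. Then bias = (s - 0.5) × d.

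| d | s = 0.3 | s = 0.5 | s = 0.7 | s = 0.9 |
|---|---|---|---|---|
| 0 | 0 | 0 | 0 | 0 |
| 10 | -2 | 0 | +2 | +4 |
| 20 | -4 | 0 | +4 | +8 |

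**4. Household size (assumed; equal-probability draw of households)**

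Take households with 1, 2 and 3 workers in equal thirds and prevalences 35 - a, 35 and 35 + a. The unweighted estimate is 35. The worker-level value is [1(35 - a) + 2(35) + 3(35 + a)] / 6 = 35 + a/3, so bias = -a/3. That is 0 for a = 0, -1.7 points for a = 5 and -3.3 points for a = 10. The sign reverses if prevalence falls with household size.

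**5. Precision cost of weighting by household size (assumed sizes)**

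Kish factor = mean of squared sizes / (mean size)²; half-width = 7.29 × √factor.

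| Sizes | Factor | Half-width | Interval |
|---|---|---|---|
| 1 and 2, 50:50 | 2.5 / 1.5² = 1.11 | 7.7 | 27.3% to 42.7% |
| 1, 2, 3 in thirds | 4.67 / 2² = 1.17 | 7.9 | 27.1% to 42.9% |
| 1 to 4 at 30/40/20/10% | 5.3 / 2.1² = 1.20 | 8.0 | 27.0% to 43.0% |

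**The case against.** The strongest reply has four parts.

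- **The limitation is disclosed.** Operational considerations and Limitations both say that probability sampling is not used at every level, and Limitations includes respondents. This stands against any suggestion of concealment. But the reasons given there (budget, funder deadline, the pandemic, accessibility) concern province and district. Neither section says that the person within the household is a volunteer, and the Fieldwork process sentence tells the reader the opposite.
- **Eligibility narrows the choice.** Only recent pesticide users can be respondents, so members who do not spray are screened out. This stands and makes large within-household contrasts less likely. It does not make two eligible workers in one household alike.
- **Bias is not shown.** A reader might infer that the prevalence estimate is biased. The documents do not support that: they give no household sizes and no within-household difference in cholinesterase, and the assumed scenarios include exactly zero. Only a risk of bias can be claimed.
- **Weighting is not ruled out.** A reader might also infer that results will be unweighted. The article is silent, and weighting is commonly left to an analysis plan that is not shown. Nor is the right weight settled. The list is of workers, so a draw on worker entries would favour larger households. Taking one person from each would roughly offset that, and a size weight would then over-correct.

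It would also be wrong to say that probability sampling is absent throughout, since households are randomised.

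**Conclusion.** The contradiction is established from the text alone: the article claims a random sample of workers and describes a random sample of households with a self-selected respondent in each. The consequence is a risk of bias in worker-level prevalences, with sign and size that cannot be derived from the documents. The range of -4 to +8 points rests on assumed differences of 0 to 20 points between two eligible workers and on assumed volunteering shares of 30% to 90%. At its upper end it is about as large as the planned half-width of 7.3 points, and the planned interval does not allow for it. The general disclosures soften the point but do not correct the sentence. It is worth changing because the list already names the regular adult farm workers, so a random step within the household is within reach.

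**What to change.** 1. After drawing households, put the listed adult workers of each household in random order. Invite and screen the first, and go to the next only if that person is ineligible or refuses. Use the reserve list once the household is exhausted.
2. Correct the sentence in Fieldwork process to match the procedure used. If the procedure stays as it is, the sentence should say that households are drawn at random and a volunteer eligible adult from each is interviewed.
3. State whether the draw is made per household or per worker entry. If per household, record the number of listed workers (and, where known, eligible workers) in each and report a prevalence weighted by that number as a sensitivity analysis.

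**Cost.** The names are already listed, so the random order itself costs little. The list does not hold recent pesticide use, so eligibility must still be found by screening in order, which means some extra contacts and refusals. Self-selection through consent remains but is reduced. The weighted estimate would have a half-width of about 7.7 to 8.0 points rather than 7.3, under the household sizes assumed above.

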## Aim and objectives

The general aim of the study is to investigate the potential health impacts of pesticides use on agricultural workers.

The specific objectives are:

To estimate the prevalence of high OPP and carbamate exposure via AChE concentrations found in agricultural workers’ capillary blood samples.To determine the proportion of workers with suboptimal behaviours that predict high exposure to pesticides.To examine workers’ health knowledge regarding pesticides-related risks, the prevalence of heath-protective behaviours, and self-reported ill health.To investigate possible associations between agricultural practices, health knowledge, health-protective practices and reports of ill-health, and the concentration of cholinesterase in capillary blood samples.

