## Materials and method

### Overview of survey and blood cholinesterase assays

Our study investigates agricultural workers’ self-reported use of pesticides, health knowledge, health protective behaviours, and health status, in combination with the measurement of pesticide exposure in capillary blood samples. Direct questioning of workers is reported to be the most common research method for assessing pesticide exposure [58], as was confirmed in our own scoping exercise [1]. In our study pesticide exposure will be assessed via measured cholinesterase concentrations using commercial field test kits (see below). Empirical fieldwork will be completed in selected localities in Thailand, Vietnam, and Lao PDR, so as to facilitate comparison of the situation in the three countries.

Researchers in each country will purposively select three suitable districts within the province in which their university is located, so that fieldwork will be conducted across 9 such districts (groups of ‘villages’ or ‘local areas’), with a target of 120 interviews per district. A researcher-administered structured interview will be used to collect data on agricultural production, health knowledge, health protective practices and behaviours, and illness episodes. Pesticides exposure will be measured as AChE concentrations in agricultural workers’ capillary blood using field test kits (described below).

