### Analysis outline

Data will be summarised using appropriate descriptive statistics; we will report on associations between agricultural methods, health knowledge, health-protective practices, self-reported illness and blood test results.

Data from each country will be analysed separately before considering whether an analysis of pooled data is appropriate.

Description of all variables: frequencies, or ranges and measures of central tendencyCombining structured interview responses to give overall measures of: outcomes, knowledge, practices/behaviours and exposures. The variables to be combined will be listed *a priori*.Measures of ill-health, knowledge, behaviours and exposures will be described separately and together.Bivariate explorations will be used to examine the variables shown in Table 1.

**Table 1 pone.0258134.t001:** Contingency tables for each comparison.

	Ill-health measures	Exposure	Practices/behaviours	Knowledge	Cholinesterase concentration
Ill-health measures					
Exposure					
Practices/behaviour					
Knowledge					
Cholinesterase concentration					

4. Multivariate analysesPrimary outcomes: AChE concentrations, ill-health measures, separately & togetherCovariates to be tested one by oneCovariates with P<0.20 will be entered into exploratory models

a) Logistic regression: high AChE concentration, any ill-health, each health issue (modelling strategy to be based on backwards LR, -2LL, VIF, check enter model)

Predictors:

1. Behaviours
a. Likely to increase exposureb. Likely to decrease exposure2. Knowledge score3. Cholinesterase concentrations (when exploring ill-health)4. Significant covariates from one-by-one testing will include: location, SES, education, literacy (ability to write), age, gender, hours worked, distance between home and farm.

Sensitivity analyses will, in turn, exclude:

Migrant workersEarlier diagnosis of pesticide poisoning

A priori sub-group analyses:

Each countrySelf-employedLowest SES or income categoryNo formal education

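### Reused Thai AChE results precede the interview while all other study tests follow it, so some Thai associations could reflect what workers already knew

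*Protocol article*

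**What the plan says.** All references are to the protocol article.

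- **Default order (Fieldwork process).** The interview comes first, then consent to blood sampling is confirmed, then the sample is taken. Where no usable health-service result exists, "finger-prick blood tests will be undertaken after the interviews".
- **Thai exception (same section).** "In Thailand local public health staff measure AChE levels of farm workers routinely as part of a government health promotion initiative". Routine testing uses identical kits, and "If tests were completed within the past 4 weeks these results will be used for this study, as was the case in the pilot study".
- **Feedback after study tests (same section, last step).** Participants who complete the blood test are told how they will be notified, and that "local health staff will advise them on necessary treatment or behavioural change".
- **What the interview measures (Overview of survey and blood cholinesterase assays).** "A researcher-administered structured interview will be used to collect data on agricultural production, health knowledge, health protective practices and behaviours, and illness episodes".
- **How the data are used.** The fourth objective (Aim and objectives) is "To investigate possible associations between agricultural practices, health knowledge, health-protective practices and reports of ill-health, and the concentration of cholinesterase in capillary blood samples". The Analysis outline lists "Logistic regression: high AChE concentration, any ill-health, each health issue", with behaviours and knowledge as predictors, and with cholinesterase as a further predictor when ill-health is the outcome.
- **Planned sensitivity analyses (Analysis outline).** These leave out, in turn, migrant workers and people previously diagnosed with pesticide poisoning. Neither separates results by source or by timing.

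**The concern.** Practices, knowledge and symptoms are self-reported. A worker who has already been told that the AChE result is low, and perhaps been advised, may answer differently from one who has not. A low result could raise reported protective practice and knowledge. The protective behaviour would then appear alongside low AChE, or a risky behaviour would look less harmful than it is. Awareness of a low result could also prompt more symptom reports and inflate the link between AChE and ill-health.

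The Reporting section says the models will identify behaviours to target, so the direction of these associations matters. The exception applies in one country only. The country comparison, the meta-analysis and any pooled model would therefore combine two orders of measurement without a marker to tell them apart.

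This point concerns the order of result and interview. How old a reused sample is relative to the last spraying is a separate matter.

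**Working it through.** **1. The order of events**

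| Participant | Order fixed by the protocol | Could a result be known at interview? |
|---|---|---|
| Default, all countries | interview, blood test, result and advice | Not from the study test |
| Thai, routine result up to 4 weeks old | routine test, interview | Possible; the article does not say |
| Thai, older routine test, retested for the study | routine test, interview, study test | Possible; the article does not say |

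The order of the tests follows from the text. The order of knowledge does not: it needs the added premise that the routine result or advice came back before the interview. The third row shows that prior knowledge would come from the routine programme and need not depend on reuse.

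**2. The plan's own precision figure, used here only as a yardstick**

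Design effect = 1 + (120 − 1) × 0.01 = 2.19, and its square root is 1.48. Half-width = 1.96 × √(2.19 × 0.35 × 0.65 / 360) = 0.073. The interval is 27.7% to 42.3%, which agrees with the 28% to 42% stated under Precision.

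**3. Possible effect on an association (illustration)**

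The 35% with low AChE is the planning figure. Everything else is assumed: 50% have a risky practice, and the true odds ratio is 1.0 or 2.0. Low AChE means the category below 75, the outcome of primary interest. Let f be the share of Thai workers whose result is reused and known before the interview. Let q be the share of those with low AChE and a risky practice who report a safer one because of the result. Then s = f × q.

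Cell proportions are a (risky, low), b (risky, not low), c (not risky, low) and d (neither).

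Observed OR = a(1 − s) × d / [b × (c + a·s)]

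- True OR 1.0: a = c = 0.175 and b = d = 0.325. With s = 0.10: 0.1575 × 0.325 / (0.325 × 0.1925) = 0.82.
- True OR 2.0: a solves a(0.15 + a) / [(0.5 − a)(0.35 − a)] = 2. This gives a = 0.21393, b = 0.28607, c = 0.13607, d = 0.36393. With s = 0.10: 0.19253 × 0.36393 / (0.28607 × 0.15747) = 1.56.

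| s | Example (f, q) | Observed if true OR is 1.0 | Observed if true OR is 2.0 |
|---|---|---|---|
| 0.025 | 25%, 10% | 0.95 | 1.88 |
| 0.05 | 50%, 10% | 0.90 | 1.76 |
| 0.10 | 50%, 20% | 0.82 | 1.56 |
| 0.15 | 50%, 30% | 0.74 | 1.38 |
| 0.20 | 100%, 20% | 0.67 | 1.22 |
| 0.30 | 100%, 30% | 0.54 | 0.95 |

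The illustration lets only workers below 75 change their answers. If those in the at-risk band (75.0–87.4) were also advised, they would change within the comparison group and the distortion would shrink.

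**4. Possible effect on prevalence (illustration)**

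A worker who stopped spraying after a low result could fail the 3-week application criterion and be replaced from the reserve list. If workers sprayed up to the result, only results about 21 to 28 days old can cause this. With tests spread evenly over 28 days, that is 7/28 = 0.25 of reused results. Assume further that 60% of results are reused and known, and that 25% of those told they are below 75 stop spraying:

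- Remaining low-AChE share: 0.35 × (1 − 0.6 × 0.25 × 0.25) = 0.337.
- Observed prevalence: 0.337 / (0.337 + 0.65) = 34.1%.

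The shift is about 0.9 points, against a half-width of 7.3 points.

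**The case against.** The strongest reply is that the order of sampling is not the order of knowledge. The article does not say that routine results or advice reach workers before the interview, and its sentence about advice describes feedback after study tests. It states no purpose for interviewing first. The fourth objective speaks only of possible associations, and the Limitations section warns against reading association as cause. In any cross-sectional survey, earlier symptoms can change behaviour in all three countries, and the planned exclusion of people with a past poisoning diagnosis covers a neighbouring route. The 83-item instrument is not shown, so it may already ask about prior testing.

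Much of this stands, and it rules out several stronger readings that a reader might infer:

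- **That the reuse rule makes Thai associations run from result to behaviour.** The text supports only a possibility, of unknown frequency.
- **That everyone outside the reuse group is naive to any result.** Thai workers with older routine tests may also have been advised, so dropping reuse would not guarantee a naive sample.
- **That prevalence is materially lowered.** With 60% reuse and 25% stopping, and with every reused result able to trigger exclusion, 0.2975 / (0.2975 + 0.65) gives 31.4%. The 3-week and 4-week windows do not normally allow that.
- **That workers without prior knowledge should form the primary Thai analysis.** With an assumed 60% reused and all known, this leaves 0.4 × 360 = 144 workers and about 50 cases (144 × 0.35). Workers whom the programme did not reach may also differ in other ways.

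The reply does not remove the point. A general caution about causation does not tell readers that one country has a different order of measurement. A routine AChE result is not a diagnosis of poisoning. Without a record of source and prior knowledge, the question cannot be examined afterwards.

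**Conclusion.** The concern holds in a limited form. The protocol fixes two orders of measurement, and only Thailand has the second. No planned analysis in the article separates them. If routine results or advice reached workers before the interview, the Thai objective 4 associations and the country comparison could be biased. For practices, the likely direction is that risky behaviour looks less harmful or protective behaviour looks harmful. For symptoms, the association with AChE may be inflated; no size is given for that here.

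The size is unknown, because neither the share of reused results nor the share known beforehand is stated. Under the assumptions above it runs from negligible (2.0 read as 1.88) to a loss of the association (2.0 read as 0.95). The effect on prevalence is likely small, about one point on the assumed figures.

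**What to change.** 1. For each Thai participant, record the source of the AChE result (routine or study), its date, and whether any AChE result and advice was known before the interview. Include routine tests older than 4 weeks. If the instrument already holds these items, confirm that they will be used.
2. Keep the full Thai sample as the main analysis.
3. Add to the sensitivity analyses in the Analysis outline one that excludes participants who knew a result before interview, or an interaction term that separates them. Apply it to the Thai association models (practices, knowledge and symptoms against AChE) and to the Thai input to the meta-analysis or pooled model.
4. State in advance that, if the estimates differ materially, the Thai associations will not be read as behaviours predicting AChE.

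The cost is one or two extra data fields and one extra analysis on a smaller, less precise Thai subset. The sample size and the prevalence analysis do not change.
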